## 9.8 Investigator Reimbursement and Contracting

BIOTRONIK will reimburse efforts undertaken for inclusion and follow up of subjects, and documentation of subject data within the study. A contract with the principal investigator and/or the respective hospital will be agreed on and signed prior to study start. Within this an overall fee per subjects broken down to individual visits will be included.

This subject fee will cover all expenses for material used and procedures to be performed according to the CIP. The CIP and any future changes thereof will be part of the contract.

## 10. PUBLICATION POLICY

BIOTRONIK intends to publish the results of this clinical investigation. BIOTRONIK reserves the right to include the report of this clinical investigation in any regulatory

documentation or submission or in any informational materials prepared for the medical profession. The ownership of the data shall at all times be held by BIOTRONIK.

Within one year after study completion a final report shall be submitted to the Member States, signed by the participating investigators of the clinical investigation. No publication of results from single center experience will be allowed until the primary endpoint is analyzed in order to allow for preparation and publication of the multicenter results.

BIOTRONIK agrees that investigators shall be permitted to present at symposia, national or regional professional meetings, and to publish in journals, thesis or dissertations, or otherwise of their own choosing, methods and results of the clinical investigation after the first publication. Any prior publication in any way or form is not permitted, without approval by BIOTRONIK.

The investigator should provide BIOTRONIK with a copy of any publication in journals, thesis or dissertations at least 4 weeks prior to submission.

## 11. APPENDICES

Appendix 1: Abbreviations

Appendix 2: Definitions

Appendix 3: "4 P" STRATEGY

## APPENDIX 1: Abbreviations

|         |                                                                 |
|---------|-----------------------------------------------------------------|
| ACH     | Acetylcholine                                                   |
| ADE     | Adverse Device Effect                                           |
| AE      | Adverse Event                                                   |
| AMI     | Acute Myocardial Infarction                                     |
| AMS     | Absorbable Metal Scaffold                                       |
| ASA     | Acetyl Salicylic Acid                                           |
| BVS     | Bioabsorbable Vascular Scaffold                                 |
| BRS     | Bio-Resorbable Scaffold                                         |
| CA      | Competent Authority                                             |
| CABG    | Coronary Artery Bypass Graft                                    |
| CI      | Confidence Interval                                             |
| CIB     | Clinical Investigator's Brochure                                |
| CIP     | Clinical Investigation Plan                                     |
| CCS     | Canadian Cardiovascular Society                                 |
| CEC     | Clinical Event Committee                                        |
| CRA     | Clinical Research Associate                                     |
| CRF     | Case Report Form                                                |
| cTn     | Cardiac troponin                                                |
| DAPT    | Dual-Antiplatelet Therapy                                       |
| DES     | Drug-Eluting Stent                                              |
| DS      | Diameter Stenosis                                               |
| DSMB    | Data Safety Monitoring Board                                    |
| DREAMS  | Sirolimus-Eluting Resorbable Coronary Magnesium Scaffold System |
| ECG     | ElectroCardioGram                                               |
| FFR     | Fractional Flow Reserve                                         |
| FIM     | First in Men (clinical study)                                   |
| FUP     | Follow UP                                                       |
| GCP     | Good Clinical Practice                                          |
| ICH     | International Conference on Harmonization                       |
| IFU     | Instructions For Use                                            |
| IRB/IEC | Institutional Review Board/Independent Ethics Committee         |
| ISO     | International Standard Organisation                             |

|       |                                                |
|-------|------------------------------------------------|
| ITT   | Intention To Treat                             |
| IVUS  | IntraVascular UltraSound                       |
| LLL   | Late Lumen Loss                                |
| LST   | Late Stent Thrombosis                          |
| MI    | Myocardial Infarction                          |
| MLD   | Minimal Luminal Diameter                       |
| OAC   | Oral Anticoagulation Therapy                   |
| OCT   | Optical Coherence Tomography                   |
| PCI   | Percutaneous Coronary Intervention             |
| PLLA  | Poly-L-Lactid Acid                             |
| PTCA  | Percutaneous Transluminal Coronary Angioplasty |
| QCA   | Quantitative Coronary Angiography              |
| RMS   | Resorbable Magnesium Scaffold                  |
| RVD   | Reference Vessel Diameter                      |
| SADE  | Serious Adverse Device Effect                  |
| SAE   | Serious Adverse Event                          |
| SOP   | Standard Operating Procedure                   |
| ST    | Stent Thrombosis                               |
| TIA   | Transient Ischemic Attack                      |
| TIMI  | Thrombolysis In Myocardial Infarction          |
| TLF   | Target Lesion Failure                          |
| TLR   | Target Lesion Revascularization                |
| TVF   | Target Vessel Failure                          |
| TVR   | Target Vessel Revascularization                |
| ULN   | Upper Limit Normal                             |
| URL   | Upper Reference Limit                          |
| US    | United States                                  |
| USADE | Unanticipated Serious Adverse Device Effect    |
| VLST  | Very Late Stent Thrombosis                     |

## APPENDIX 2: Definitions

### ACUTE GAIN

Acute gain was defined as the immediate dimensional change in minimal luminal diameter (in mm) that occurred after the final post-dilatation as compared to the minimal luminal diameter at baseline and measured by quantitative coronary angiography from the average of 2 orthogonal views.

### BRAUNWALD CLASSIFICATION (127)

| Severity |                                                                | Clinical circumstances in which unstable angina occurs                                                           |                                                                          |                                                               |
|----------|----------------------------------------------------------------|------------------------------------------------------------------------------------------------------------------|--------------------------------------------------------------------------|---------------------------------------------------------------|
|          |                                                                | A                                                                                                                | B                                                                        | C                                                             |
|          |                                                                | Develops in Presence of Extra cardiac Condition That Intensifies Myocardial Ischemia (Secondary Unstable Angina) | Develops in Absence of Extra cardiac Condition (Primary Unstable Angina) | Develops Within 2 wk of AMI (Post infarction Unstable Angina) |
| I        | New onset of severe angina or accelerated angina; no rest pain | IA                                                                                                               | IB                                                                       | IC                                                            |
| II       | Angina at rest within past month but not within preceding 48 h | IIA                                                                                                              | IIB                                                                      | IIC                                                           |

|     |                                                    |      |                                                              |      |
|-----|----------------------------------------------------|------|--------------------------------------------------------------|------|
|     | (angina at rest, sub-acute)                        |      |                                                              |      |
| III | Angina at rest within 48 h (angina at rest, acute) | IIIA | IIIB-Troponin neg
IIIB-Troponin pos | IIIC |

### CARDIOGENIC SHOCK (CS) (128)

Cardiogenic shock (CS) is a state of end-organ hypoperfusion due to cardiac failure. The definition of CS includes hemodynamic parameters: persistent hypotension (systolic blood pressure < 80 to 90 mm Hg or mean arterial pressure 30 mm Hg lower than baseline) with severe reduction in cardiac index (< 1.8 L x min x m^-2 without support or < 2.0 to 2.2 L x min x m^-2 with support) and adequate or elevated filling pressure (eg, left ventricular end-diastolic pressure > 18 mm Hg or right ventricular end-diastolic pressure > 10 to 15 mm Hg)

### CANADIAN CARDIOVASCULAR SOCIETY (CCS) ANGINA CLASSIFICATION (129,130)

| Class | Definition                                                                                                                                                                                                          |
|-------|---------------------------------------------------------------------------------------------------------------------------------------------------------------------------------------------------------------------|
| I     | Ordinary physical activity does not cause angina such as walking, climbing stairs. Angina (occurs) with strenuous, rapid, or prolonged exertion at work or recreation.                                              |
| II    | Slight limitation of ordinary activity. Angina occurs on walking or climbing stairs rapidly, walking uphill; walking or stair climbing after meals, in cold, in wind, or under emotional stress, or only during the |

|     |                                                                                                                                                                                       |
|-----|---------------------------------------------------------------------------------------------------------------------------------------------------------------------------------------|
|     | few hours after awakening; Angina occurs on walking more than 2 blocks on the level and climbing more than one flight of ordinary stairs at a normal pace and in normal conditions.   |
| III | Marked limitation of ordinary physical activity. Angina occurs on walking one to two blocks on the level and climbing one flight of stairs in normal conditions and at a normal pace. |
| IV  | Inability to carry on any physical activity without discomfort - angina symptoms may be present at rest.                                                                              |

#### DE NOVO LESION

A native coronary artery lesion not previously treated.

#### DEATH ACCORDING TO ARC-1 DEFINITION (131)

|                    |                                                                                                                                                                                                                                                                  |
|--------------------|------------------------------------------------------------------------------------------------------------------------------------------------------------------------------------------------------------------------------------------------------------------|
| Cardiac death      | Any death due to proximate cardiac cause (e.g., MI, low-output failure, fatal arrhythmia), unwitnessed death and death of unknown cause and all procedure-related deaths, including those related to concomitant treatment, will be classified as cardiac death. |
| Vascular death     | Death caused by non-coronary vascular causes, such as cerebrovascular disease, pulmonary embolism, ruptured aortic aneurysm, dissecting aneurysm, or other vascular diseases.                                                                                    |
| Non-cardiovascular | Any death not covered by the above definitions, such                                                                                                                                                                                                             |

|                                                                                                                                                                                                                                                                           |                                                                                                   |
|---------------------------------------------------------------------------------------------------------------------------------------------------------------------------------------------------------------------------------------------------------------------------|---------------------------------------------------------------------------------------------------|
| death                                                                                                                                                                                                                                                                     | as death caused by infection, malignancy, sepsis, pulmonary causes, accident, suicide, or trauma. |
| 
All deaths are considered cardiac unless an unequivocal non-cardiac cause can be established. Specifically, any unexpected death even in subjects with coexisting potentially fatal non-cardiac disease (e.g., cancer, infection) should be classified as cardiac.
 |                                                                                                   |

## DEATH ACCORDING TO ARC-2 DEFINITION (132)

| Type of death            | Definition                                                                                                                                                                                                                                                                                                                                                                                                                                                                                                                                                                                                |
|--------------------------|-----------------------------------------------------------------------------------------------------------------------------------------------------------------------------------------------------------------------------------------------------------------------------------------------------------------------------------------------------------------------------------------------------------------------------------------------------------------------------------------------------------------------------------------------------------------------------------------------------------|
| Cardiovascular           | 
Cardiovascular death as defined as death resulting from cardiovascular causes. The following categories may be collected:
 
 
1) Death caused by acute MI
 
2) Death caused by sudden cardiac, including unwitnessed death
 
3) Death resulting from heart failure
 
4) Death caused by stroke
 
5) Death caused by cardiovascular procedure
 
6) Death resulting from cardiovascular haemorrhage
 
7) Death resulting from other cardiovascular causes
 
                                                    |
| Non-cardiovascular death | 
Non-cardiovascular death is defined as any death that is not thought to be the result of a cardiovascular cause. The following categories may be collected:
 
 
1) Death resulting from malignancy
 
2) Death resulting from pulmonary cause
 
3) Death caused by infection (including sepsis)
 
4) Death resulting from gastrointestinal causes
 
5) Death resulting from accident/trauma
 
6) Death caused by non-cardiovascular organ failure
 
7) Death resulting from other non-cardiovascular causes
 
 |

|              |                                                                                                                                                                                                                                 |
|--------------|---------------------------------------------------------------------------------------------------------------------------------------------------------------------------------------------------------------------------------|
| Undetermined | Undetermined cause of death is defined as a death non attributable for any other category because of the absence of any relevant source documents. Such deaths will be classified as cardiovascular for endpoint determination. |
|--------------|---------------------------------------------------------------------------------------------------------------------------------------------------------------------------------------------------------------------------------|

## DEVICE SUCCESS

Device Success is defined as a final residual diameter stenosis of <30% by QCA, using the assigned device only

- successful delivery of the scaffold to the target lesion site in the coronary artery
- appropriate scaffold deployment
- successful removal of the device
- safe removal of the device in case of deployment failure

The definition is based on the EU guideline on medical devices from 2015 (MeDDev 2.7.1 Appendix 1).

## DEVICE AND /OR PROCEDURE CAUSALITY ASSESSMENT

The following definitions will be used to assess the relationship of the adverse event to the investigational medical device or to the study procedures:

1) Not related: relationship to the device or procedures can be excluded when:

- the event is not a known side effect of the product category the device belongs to or of similar devices and procedures;
- the event has no temporal relationship with the use of the investigational device or the procedures;
- the serious event does not follow a known response pattern to the medical device (if the response pattern is previously known) and is biologically implausible;
- the discontinuation of medical device application or the reduction of the level of activation/exposure - when clinically feasible – and reintroduction of its use (or increase of the level of activation/exposure), do not impact on the serious event;
- the event involves a body-site or an organ not expected to be affected by the device or procedure;
- the serious event can be attributed to another cause (e.g. an underlying or concurrent illness/ clinical condition, an effect of another device, drug, treatment

or other risk factors);

- the event does not depend on a false result given by the investigational device used for diagnosis, when applicable;
- harms to the subject are not clearly due to use error;
- In order to establish the non-relatedness, not all the criteria listed above might be met at the same time, depending on the type of device/procedures and the serious event.

2) Unlikely: the relationship with the use of the device seems not relevant and/or the event can be reasonably explained by another cause, but additional information may be obtained.

3) Possible: the relationship with the use of the investigational device is weak but cannot be ruled out completely. Alternative causes are also possible (e.g. an underlying or concurrent illness/ clinical condition or/and an effect of another device, drug or treatment). Cases where relatedness cannot be assessed or no information has been obtained should also be classified as possible.

4) Probable: the relationship with the use of the investigational device seems relevant and/or the event cannot be reasonably explained by another cause, but additional information may be obtained.

5) Causal relationship: the serious event is associated with the investigational device or with procedures beyond reasonable doubt when:

- the event is a known side effect of the product category the device belongs to or of similar devices and procedures;
- the event has a temporal relationship with investigational device use/application or procedures;
- the event involves a body-site or organ that
  - o the investigational device or procedures are applied to;
  - o the investigational device or procedures have an effect on;
- the serious event follows a known response pattern to the medical device (if the response pattern is previously known);
- the discontinuation of medical device application (or reduction of the level of

- activation/exposure) and reintroduction of its use (or increase of the level of activation/exposure), impact on the serious event (when clinically feasible);
- other possible causes (e.g. an underlying or concurrent illness/ clinical condition or/and an effect of another device, drug or treatment) have been adequately ruled out;
  - harm to the subject is due to error in use;
  - the event depends on a false result given by the investigational device used for diagnosis, when applicable;
  - In order to establish the relatedness, not all the criteria listed above might be met at the same time, depending on the type of device/procedures and the serious event.

### **PERCENT DIAMETER STENOSIS**

Mean lumen diameter divided by the reference vessel diameter times one hundred

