#### 4.8 Secondary Endpoints

##### Clinical

- Target Lesion Failure (TLF\*) at 1, 6, 12, and annually up to 36 months follow up

- Cardiac death at 1, 6, 12, and annually up to 36 months follow up (according to ARC-1 definition)
- Target vessel MI at 1, 6, 12, and annually up to 36 months follow up\*\*
- Clinically driven target lesion revascularization at 1, 6, 12, and annually up to 36 months follow up
- Clinically driven target vessel revascularization at 1, 6, 12, and annually up to 36 months follow up
- Definite and probable scaffold thrombosis rate at at 1, 6, 12, and annually up to 36 months follow up (according to ARC-2 definition)
- Procedure success: achievement of a final diameter stenosis of <30% by QCA, using any percutaneous method, without the occurrence of death, Q-wave or non-Q-wave MI, or repeat revascularization of the target lesion during the hospital stay.
- Device Success: final residual diameter stenosis of <30% by QCA, or visual assessment using the assigned device only with:
  - Successful delivery of the scaffold to the target lesion
  - Appropriate scaffold deployment
  - Successful removal of the delivery system

\*defined according to ARC-2 and ARC-1 definition.

\*\* periprocedural MIs will be adjudicated according to SCAI-definitions and ARC-2 definitions

Secondary clinical endpoints were selected as per recommendations of the American College of Cardiology (ACC) and the American Heart Association (AHA) (Ref. ACC/AHA CLINICAL DATA STANDARDS: "", JACC VOL2014 ACC/AHA Key Data Elements and Definitions for Cardiovascular Endpoint Events in Clinical Trials. 66, NO. 4, 2015) (119).

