### Angiographic

- In-segment late lumen loss at 6 months
- In-scaffold and in-segment late lumen loss at 12 months
- Binary in-scaffold and in-segment restenosis rate at 6 and 12 months
- % in-scaffold and in-segment diameter stenosis at 6 and 12 months

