#### 5.12.5 Vasomotion

If subject consents, a vasomotion test will be performed at 12 months follow up in order to obtain additional information on vasoreactivity of the vessel as well as vessel movement throughout absorption of the DREAMS 3G.

All anti-anginal agents that influence vasomotor tone, including long-acting nitrate, calcium-channel blockers, and beta-blockers, should be withheld for at least 48 h before coronary angiography, except for sublingual nitroglycerin as needed.

A coronary angiography will be taken prior to injection of acetylcholine (ACH) in the same two orthogonal views used during baseline procedure.

Diagnostic left / right heart catheterization and coronary angiography will be performed by a standard percutaneous approach. A 6-F diagnostic catheter will be introduced into the left main or right coronary artery, depending on the vessel studied. To ensure that the segments were fully bathed by the infusion of acetylcholine (ACH), the tip of the infusion catheter will be placed 8 -12 mm proximal to the proximal border of the scaffolded segment. To avoid wire induced coronary spasm, the wire will be removed.

Vasomotor reactivity will be estimated by infusing incremental doses of ACH into the coronary artery using an infusion catheter (i.e. Finecross MG; Terumo).

ACH should be admitted in different concentration.

- ACH1 (low dose): 0.36 µg/mL
- ACH2 (middle dose): 3.6 µg/mL
- ACH3 (high dose): 18 µg/mL

Speed of infusion should be 2 mL/min. Duration of infusion should be around 3 minutes. Contrast injection should be filmed after 3 minutes of i.c. infusion of ACH.

When the maximum dose is reached, an intracoronary bolus injection of nitroglycerin (200 µg) will be administered followed immediately by angiography in the same two orthogonal views used during baseline procedure.

Throughout each infusion, the heart rate, systemic arterial pressure, and ECG will be monitored continuously

End-diastolic images for each segment will be chosen and analyzed with the automated edge detection program by QCA. The scaffolded segment and the 5-mm proximal and distal to the site of scaffolding will be studied. Changes in coronary diameter in response to ACH and nitrate coronary infusion will be expressed as percent changes versus baseline angiograms. The mean lumen diameters will be measured by QCA

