### LATE LUMEN LOSS (LLL)

Post-procedure minimal lumen diameter (MLD) minus follow-up MLD as determined by quantitative angiography.

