## MINIMAL LUMINAL DIAMETER (MLD)

Mean minimum lumen diameter derived from two orthogonal views (by the quantitative coronary angiography laboratory)

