## REFERENCE VESSEL DIAMETER (RVD)

The interpolated reference vessel diameter is based on a computed estimation of the original diameter of the artery at the level of the obstruction (minimal luminal diameter)

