**CLINICALLY DRIVEN TARGET LESION REVASCULARIZATION (TLR) (123)**

Any clinically-driven repeat percutaneous intervention of the target lesion including 5mm proximal and 5mm distal from the edge of the scaffold, or bypass surgery of the target vessel that was performed for a clinical indication and was due to restenosis or closure of the target lesion.

Clinically-driven revascularizations are those in which the subjects has a positive functional clinical investigation, ischemic ECG changes at rest in a distribution consistent with the target vessel, or ischemic symptoms and an in-lesion diameter stenosis  $\geq 50\%$  by QCA. Revascularization of a target lesion with an in-lesion diameter stenosis  $\geq 70\%$  (by QCA) in the absence of the above-mentioned ischemic signs or symptoms is also considered clinically-driven. In the absence of QCA data for relevant follow-up angiograms, the clinical need for revascularization is adjudicated using the presence or absence of ischemic signs and symptoms.

Non-clinically driven repeat target lesion revascularizations are those in which the subjects undergoes a non-emergent revascularization for a diameter stenosis  $< 50\%$  (by QCA). Non-emergent repeat target lesion revascularization for a diameter stenosis  $< 70\%$  (by QCA) in subjects without either a positive functional clinical investigation or angina are also considered non-clinically driven.

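### Appendix 2 defines percent diameter stenosis as the open share of the vessel, and on the mean rather than the minimal lumen; read literally, this inverts a secondary endpoint and the QCA-based cut-offs

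*Protocol*

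**What the plan says.** Appendix 2, Percent Diameter Stenosis, consists of one complete sentence: "Mean lumen diameter divided by the reference vessel diameter times one hundred". No other section corrects or qualifies it.

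The quantity is used in these places:

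- **Section 4.8, Angiographic:** a secondary endpoint is the percentage "in-scaffold and in-segment diameter stenosis at 6 and 12 months". Binary restenosis at the same visits is listed next to it, without a numeric cut-off.
- **Section 4.8, Clinical:** procedure success requires "achievement of a final diameter stenosis of <30% by QCA". Device success uses the same 30% limit, by QCA or by visual assessment. Appendix 2 repeats both success definitions, and its device success entry mentions QCA only.
- **Appendix 2, Clinically Driven TLR:** the QCA threshold is 50% with ischaemic signs or symptoms. "Revascularization of a target lesion with an in-lesion diameter stenosis" of at least 70% counts as clinically driven without them. When no QCA is available, signs and symptoms decide. Clinically driven TLR is a component of TLF under both the ARC-1 and the ARC-2 definition.

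The neighbouring definitions rest on the minimal lumen. MLD is the "Mean minimum lumen diameter derived from two orthogonal views". Late lumen loss (LLL) is "Post-procedure minimal lumen diameter (MLD) minus follow-up MLD as determined by quantitative angiography". Acute gain is a change in minimal luminal diameter, and RVD is interpolated at the site of the minimal luminal diameter.

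**The concern.** Two things are wrong in the one sentence. First, the complement is missing: lumen divided by reference is high in an open vessel and low in a narrowed one. Every other use of stenosis in the protocol runs the other way. Success lies below 30%, the TLR thresholds are lower bounds, and inclusion criterion 7 places the upper end of the scale at 100%. Second, the diameter named is the mean lumen diameter, which elsewhere in the protocol is the vasomotion measurement (Section 5.12.5: "The mean lumen diameters will be measured by QCA").

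At stake are one listed secondary endpoint and the QCA-based classification of procedure success, device success and clinically driven TLR. An SAP or an adjudication charter that copies the sentence inherits the error. One that uses the usual formula departs from the protocol's definition.

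**Working it through.** The protocol gives no worked value of percent diameter stenosis, so there is no figure to reproduce. The check compares the printed formula with the one that the protocol's own cut-offs require.

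**Inputs.** The printed definition, the MLD and RVD definitions and the TLR cut-offs (≥50%, ≥70%) come from Appendix 2. The success cut-off (<30%) comes from Section 4.8 and Appendix 2. The diameters below are assumed for illustration; the protocol gives none.

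**Formulas.**

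- As printed: P = 100 × D / RVD, with D the lumen diameter.
- As the cut-offs require: S = 100 × (1 − MLD / RVD).

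**Step 1: the inversion alone.** Put D = MLD. Then P = 100 − S for any RVD.

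| True stenosis S | MLD if RVD = 3.0 mm | As printed, P |
|---|---|---|
| 0% | 3.0 mm | 100% |
| 10% | 2.7 mm | 90% |
| 20% | 2.4 mm | 80% |
| 50% | 1.5 mm | 50% |
| 70% | 0.9 mm | 30% |
| 100% | 0 mm | 0% |

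Each cut-off, applied to P, then means:

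- P < 30% selects S > 70%, so a result with 10% residual stenosis fails success and an occlusion meets the stenosis limit;
- P ≥ 50% selects S ≤ 50%;
- P ≥ 70% selects S ≤ 30%.

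**Step 2: the diameter.** Suppose the inversion is fixed but the mean lumen stays in the formula. With RVD = 3.0 mm and three assumed lesions:

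| MLD | Mean lumen | (1 − MLD/RVD) × 100 | (1 − mean/RVD) × 100 | As printed |
|---|---|---|---|---|
| 1.4 mm | 2.1 mm | 53.3% | 30.0% | 70.0% |
| 2.0 mm | 2.5 mm | 33.3% | 16.7% | 83.3% |
| 2.6 mm | 2.85 mm | 13.3% | 5.0% | 95.0% |

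The first lesion crosses the 50% TLR threshold and the second crosses the 30% success limit on the choice of diameter alone. The third crosses neither. Restoring the complement is therefore not enough; the minimum has to be restored too.

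**Step 3: what does not depend on the definition.** The primary endpoint and the powered 12-month endpoint are in-scaffold LLL, a difference of two MLDs. The sample size in Section 7.2 uses only the margin (0.145 mm), the SDs (0.34 and 0.35 mm), alpha, power and dropout. A one-sample one-sided t-test at alpha 0.025 and power 0.95 reproduces the plan's figures: 74 evaluable, 74 / 0.85 = 87.1, rounded up to 88; and 78 evaluable, 78 / 0.75 = 104. Percent diameter stenosis enters none of this.

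**The case against.** The strongest reply is that this is an obvious drafting slip with little practical risk. Images are read by an independent core laboratory under its own written guidelines (Section 8.2), and events are finally adjudicated by the Clinical Events Committee (Section 8.1.2). A definition that scores a wide-open vessel near 100% conflicts so plainly with the thresholds that a reader would notice. The diameter may also be a slip rather than a choice: the MLD entry itself begins with the word for mean, so dropping one word would produce the printed phrase.

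Much of this stands as to likelihood. The core laboratory would probably apply the conventional formula, and nothing shows that the mean lumen was chosen on purpose. It does not make the sentence right. The protocol fixes the definition of a listed endpoint, and the core-laboratory guidelines and SAP are not at hand to show that they override it.

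Some stronger readings are tempting but not supported:

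- **That every criterion with a stenosis cut-off is wrong.** Visual eligibility estimates, the visual route to device success in Section 4.8, and TLR adjudicated without QCA do not run through the formula.
- **That good results would be labelled restenosis.** The protocol states no cut-off for binary restenosis, so the effect there is in principle only.
- **That TLF as a whole is reversed.** Its death and myocardial infarction components, and emergent bypass surgery in the ARC-1 version, do not use the formula.
- **That the main result is at risk.** LLL and the sample size do not depend on the formula.

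**Conclusion.** The definition is wrong as written. Read literally, it returns 100 minus the true stenosis when MLD is the diameter: 90% for a true 10%, and 0% for an occlusion. It thereby inverts percent diameter stenosis at 6 and 12 months and reverses the QCA-based cut-offs for procedure success, device success and clinically driven TLR, hence the TLR component of TLF. With the mean lumen in the numerator the values also depend on lesion shape and can move a lesion across a cut-off even once the direction is corrected; the size of that second effect rests on assumed diameters.

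The primary endpoint, the powered 12-month LLL endpoint and the sample size are unaffected. This is an error in the written definition of QCA-based secondary endpoints. The protocol does not show that measurements have been or will be made that way.

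**What to change.** Replace the sentence under Percent Diameter Stenosis in Appendix 2 with:

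*% diameter stenosis = (1 − MLD/RVD) × 100, with MLD as defined under Minimal Luminal Diameter and RVD as defined under Reference Vessel Diameter.*

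Then confirm that the core-laboratory guidelines and the SAP use the same formula. Leave the existing cut-offs and the visual-assessment route to device success unchanged. Requiring core-laboratory QCA for every success endpoint would be a separate change that this error does not call for.

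The cost is one line in the appendix and a cross-check of two documents. No hypothesis, margin, sample size or clinical rule changes.
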